#### Secondary outcome measures

The secondary outcomes measures will be (i) motor performance (lower limb motricity, gait, and balance), (ii) cognitive performance, (iii) autonomy, (iv) disability, and (v) QoL in the short, medium, and long terms after stroke, as a function of gait characteristics. In order to evaluate short-, medium- and long-term effects, these outcomes will be assessed at M1, M2, and M6, respectively.

Pre-study training visits will ensure that each center's personnel are trained in the study requirements, standardized measurement, counseling for adherence, and the collection of information from the study participants in a uniform, reproducible manner. The data will be collected in an electronic case report form (e-CRF), and the procedures to be implemented at each visit will be reviewed in detail in the SYNCOMOT manual. Each of the data collection forms and the nature of the required information will be discussed in detail on an item-by-item basis. Entering data forms, responding to data discrepancy queries, and obtaining research-quality data will also be covered during the training session.

The study manual will include details of SYNCOMOT's procedures and the equipment used, in order to standardize clinical practice during the assessments at M0, M1, M2, and M6. Manuals and monitoring visits will increase the data quality and ensure that the centers will not deviate from the protocol.

Data from the e-CRF will be securely transmitted and quality controlled in the same manner as the core data from the coordinating center. Ennov Clinical® data entry software will instantly identify any missing or aberrant data, so that the latter can be completed or corrected as soon as possible.

### Plans to promote participant retention and complete follow-up {18b}

SYNCOMOT is an in-patient protocol; retention is therefore expected to be high because (i) the included patients will be hospitalized in a stroke rehabilitation unit during their GR, and (ii) follow-up at M6 is a routine clinical procedure after stroke. Any deviation from the study protocols will be reported in the e-CRF by training therapists. The Ennov Clinical® data entry software will instantly identify any missing or aberrant data, so that the latter can be completed or corrected as soon as possible. This multicenter, randomized, controlled superiority trial will compare DT versus ST GR programs for all allocated patients with available data, on an intention-to-treat basis.

### Data management {19}

Therapists will collect data on paper CRFs and will then enter the data into an Ennov Clinical® e-CRF. Data quality will be enhanced by the application of Ennov Clinical® data capture software and monitoring visits (with checks on data entry, coding, security, and storage).

### Confidentiality {27}

The study database will be pseudo-anonymized (with assignment of patient codes) and held on a server with a secure sockets layer certificate, in order to protect confidentiality before, during, and after the trial. The patient-information leaflet will state that the study data will be stored for 15 years. The personal data will be accessible only to the coordinating investigator, the relevant health authorities (for official inspections), or representatives duly appointed by the sponsor (for quality audits).

### Plans for collection, laboratory evaluation, and storage of biological specimens for genetic or molecular analysis in this trial/future use {33}

Not applicable.

## Statistical methods

### Statistical methods for primary and secondary outcomes {20a}

#### Primary outcome measure

The primary outcome measure will be the ST 10MWT result 5 months after the end of the GR protocol. Depending on the type of data and after adjustment for the patient’s age, center and the NIHSS score in an analysis of covariance (ANCOVA), an independent *t*-test, a Mann-Whitney test, or a generalized linear mixed model will be used to compare the two groups with regard to the 10MWT speed.

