**Methods:**

This multicenter (*n*=12), two-arm, parallel-group, randomized (1:1), controlled clinical study is a superiority trial. With *p*<0.05, a power of 80%, and an expected loss to follow-up rate of 10%, the inclusion of 300 patients will be required to evidence a 0.1-m.s^−1^ gain in gait speed. Trial will include adult patients (18–90 years) in the subacute phase (0 to 6 months after a hemispheric stroke) and who are able to walk for 10 m (with or without a technical aid). Registered physiotherapists will deliver a standardized GR program (30 min three times a week, for 4 weeks). The GR program will comprise various DTs (phasic, executive function, praxis, memory, and spatial cognition tasks during gait) in the DT (experimental) group and gait exercises only in the ST (control) group. The primary outcome measure is gait speed 6 months after inclusion. The secondary outcomes are post-stroke impairments (National Institutes of Health Stroke Scale and the motor part of the Fugl-Meyer Assessment of the lower extremity), gait speed (10-m walking test), mobility and dynamic balance (timed up-and-go test), ST and DT cognitive function (the French adaptation of the harmonization standards neuropsychological battery, and eight cognitive-motor DTs), personal autonomy (functional independence measure), restrictions in participation (structured interview and the modified Rankin score), and health-related quality of life (on a visual analog scale). These variables will be assessed immediately after the end of the protocol (probing the short-term effect), 1 month thereafter (the medium-term effect), and 5 months thereafter (the long-term effect).

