### Eligibility criteria {10}

The inclusion criteria will be as follows: (i) age between 18 and 90, (ii) admission to a rehabilitation department within 6 months of a first ischemic or hemorrhagic stroke with positive brain imaging findings (computed tomography (CT) or magnetic resonance imaging (MRI) of the brain), (iii) ability to provide informed consent, (iv) ability to walk at least 10 m (with or without a technical aid) at a speed below 1.2 m.s^−1^, and (v) social security coverage. The exclusion criteria will be (i) prestroke locomotor or neurological disorders affecting gait, (ii) visual or hearing disorders that impair communication, (iii) severe aphasia, (iv) participation in another interventional study of gait or cognitive rehabilitation, (v) pregnancy or breastfeeding, and (vi) administrative supervision (legal guardianship or incarceration).

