### Outcomes {12}

#### Clinical assessments at baseline (Table 3)

The study population's characteristics recorded at baseline (M0) will include demographic variables (age, sex, and handedness), comorbidities (neuro-orthopedic and bladder disorders), the stroke date, the type of stroke (site, side, and ischemic or hemorrhagic), the stroke severity (National Institutes of Health Stroke Scale (NIHSS) score) [47], neurological impairment (the motor part of the Fugl-Meyer Assessment of the lower extremity [54], the French adaptation of the Harmonization Standards Neuropsychological Battery [50, 55, 56] (Table 4), personal autonomy (the functional independence measure (FIM) [51]), disability (a structured interview with a modified Rankin scale score (mRS-SI) (Table 5) [52]); and QoL on a VAS (QoL-VAS). Qualitative and quantitative gait variables will be assessed with a clinical classification of gait disorders (Supplementary material 1), the single-task 10-m walking test (ST 10MWT) [61], and the FIM's “walking” item [51]. Balance will be assessed in the timed up-and-go (TUG) test. In order to assess CMI, four cognitive-motor DTs will be performed during the DT 10MWT and the DT TUG test: a verbal Trail Making Test (executive function) [59], a symbolic praxis test [60], a literal fluency test [50], and a verbal serial number recall task (short-term memory [62]). The data from the cognitive-motor DTs will be recorded every 15 s, so that participants can be compared regardless of their gait speed [63].

**Table 3 Tab3:** Schedule for the assessment of primary and secondary outcomes

	Recruitment	Inclusion M0	Follow-up visit at M1	Follow-up visit at M2	Follow-up visit at M6

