## Assignment of interventions: allocation

### Sequence generation {16a}

The randomization procedure will be prepared by a data manager in the Clinical Research and Innovation Directorate (*Direction de la Recherche Clinique et de l'Innovation*, DRCI) at Amiens Picardie University Medical Center and implemented using Ennov Clinical® electronic data capture software (version 8.0.140, Ennov, Paris, France). The participants will be randomized (1:1) after inclusion and the baseline screening assessments at M0. To obtain groups that are balanced with regard to the stroke prognosis, stroke severity, and center, participants will be stratified by age (<45, 45 to 64, and ≥65), severity (according to the NIHSS score: < 5, 6 to 24, and ≥25), and center (1 to 12).

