#### Secondary outcome measures

After adjustment for the patient’s age, center, and NIHSS score (in an ANCOVA), an independent *t*-test or a Mann-Whitney test will be used to assess intergroup differences in the secondary outcomes: motor skills (including lower limb motricity: the motor part of the Fugl-Meyer Assessment of the lower extremity), gait (10MWT), ambulation capacity (FIM) and balance (TUG)), cognitive skills (neuropsychological assessments of the French validated battery for stroke), personal autonomy (FIM), disability (mRS-SI), and QoL-VAS. As appropriate, Pearson’s correlation coefficient or Spearman's correlation coefficient (r) will be used to assess performance in gait and balance DTs (eight cognitive-motor DTs: phasic, executive, praxis, memory DT 10MWT and DT TUG tasks) and (in a univariate analysis) to identify cognitive and motor determinants correlated with an increment in ST 10MWT speed. We shall rule out multicollinearity by applying standard procedures. Multiple linear regression will then be used to identify factors that are independently correlated with an increment in gait speed.

Between-group comparisons at baseline will be performed using a t-test, a Mann-Whitney test, a Kruskal–Wallis test, a chi-squared test, or Fisher’s exact test, as appropriate. Statistically significant group interactions and factors will be analyzed post hoc. The Bonferroni method will be used to adjust the overall level of significance for multiple testing. All statistical analyses will be performed using SAS software (version 9.3, SAS institute Inc, Cary, NC, USA). The threshold for statistical significance will be set to *p*<0.05. A statistician blinded to the study group assignment will perform the statistical analyses.

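### The stated covariate list omits time since stroke, although the stroke date is recorded: a modest precision loss for the randomized comparison, and a confounding risk in the regression of gait-speed increment

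*Protocol article*

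**What the plan says.** **Entry window.** The Abstract (Methods) takes patients "in the subacute phase (0 to 6 months after a hemispheric stroke". Eligibility criteria {10} requires "admission to a rehabilitation department within 6 months of a first ischemic or hemorrhagic stroke" and sets no narrower limit for inclusion.

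**Data collected.** Clinical assessments at baseline lists "the stroke date, the type of stroke" among the M0 variables. Table 3 also schedules the single-task 10MWT at M0.

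**Allocation.** Sequence generation {16a} states its aim as "To obtain groups that are balanced with regard to the stroke prognosis, stroke severity, and center". The factors used are age (3 levels), NIHSS (3 levels) and center (12).

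**Analysis.** Under Statistical methods {20a}, the primary outcome is adjusted for "age, center and the NIHSS score in an analysis of covariance (ANCOVA". The secondary outcomes get the same three covariates. A separate analysis screens cognitive and motor variables for correlation with the gain in 10MWT speed, and then: "Multiple linear regression will then be used to identify factors that are independently correlated with an increment in gait speed". Time since stroke is named in none of these places.

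**Timing of the endpoint.** The Abstract counts month 6 from inclusion, and {20a} counts five months from the end of the program. Outcomes {12} and Plans for assessment {18a} count month 6 from the stroke.

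**The concern.** A patient who enters two weeks after stroke has most spontaneous recovery still to come; one who enters near six months has little. The trial is built on starting in the recovery window, yet a patient's position in that window is left unexplained.

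Two analyses are affected in different ways. In the randomized comparison, a prognostic variable left out of the model stays in the residual variance and widens the interval. In the increment regression the predictors are not randomized. The amount gained depends on how much recovery remains, and impairment measured at entry may depend on how recent the stroke is. A score that only marks early entry could then be reported as an independent determinant of recovery.

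**Working it through.** **1. The plan's own figure.** Inputs from Sample size {14}: difference 0.1 m/s, SD 0.3 m/s, two-sided alpha 0.05, power 80%.

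n per group = 2 × (1.960 + 0.842)² × 0.3² / 0.1² = 141.3, so 142 per group and 284 in total. The stated 280 reproduces to within 1.4%. Power is 79.6% at 280. With 300 included less 10% (Recruitment {15}), 270 are evaluable (135 per group) and power is 78.2%.

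**2. What entry time does to month-6 speed.** The primary outcome is a speed level, not a gain. Assumptions: everyone follows one recovery curve f, entry is uniform over days 0 to 180, the outcome falls 180 days after entry, and the total rise over 360 days is 0.50 m/s. Let a be the rise over days 0–180 and b the rise over days 180–360, so a + b = 0.50. The remaining gain is a for the earliest entrant and b for the latest. The spread in month-6 speed across entry times is f(360) − f(180) = b. Speed is taken as roughly linear within that range, so SD = b/√12.

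| Fall in remaining gain, a − b | a | b | SD of month-6 speed due to entry time | Share of 0.3² |
|---|---|---|---|---|
| 0.50 | 0.50 | 0 | 0 | 0% |
| 0.25 | 0.375 | 0.125 | 0.125/√12 = 0.036 | 0.0013/0.09 = 1.4% |

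Early entrants gain more but start lower, and in the month-6 level the two largely cancel. The 1.4% is not a hard ceiling: a rise that did not slow at all (a = b = 0.25) would give 0.25/√12 = 0.072 m/s, or 5.8%.

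**3. Chance imbalance on the same curve.** SD of entry time = 180/√12 = 52 days. With 140 per group, the 95% range of the difference in means = 1.96 × 52 × √(2/140) = ±12.2 days. With b = 0.125, the shift is 12.2 × 0.125/180 = 0.0085 m/s. The standard error of the group difference is 0.3 × √(2/140) = 0.036 m/s and already contains this variation.

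**4. Power if the added adjustment removes a share R2 of the variance.** Residual SD = 0.3 × √(1 − R2), 270 evaluable. The documents give no R2, so this range is an assumption.

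| R2 | Residual SD | Power | Evaluable N for 80% |
|---|---|---|---|
| 0 | 0.300 | 78.2% | 284 |
| 0.02 | 0.297 | 79.0% | 278 |
| 0.05 | 0.292 | 80.2% | 270 |
| 0.10 | 0.285 | 82.3% | 256 |
| 0.20 | 0.268 | 86.5% | 228 |

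Step 2 places time since stroke alone at or below the first non-zero row. Higher rows become plausible mainly once baseline speed is in the model: at a fixed baseline speed, expected month-6 speed differs by the remaining gain, and the offset disappears.

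**5. The increment regression.** Here the outcome is the gain itself. On the same curve the expected gain differs by a − b = 0.25 to 0.50 m/s between earliest and latest entry, an SD of 0.072 to 0.144 m/s. The documents give no variance for the increment, so this cannot be turned into a share. It does show that the variable which nearly cancels in the month-6 level does not cancel here.

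**The case against.** **Randomization protects the primary test.** This stands. Omitting a prognostic covariate does not bias the comparison. A reader might infer that an imbalance in entry time could pass for a treatment effect, but chance imbalance is already inside the standard error.

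**The effect may be tiny.** This also largely stands. A reader might divide the spread in remaining gain (SD 0.072 to 0.144 m/s) by the planned variance of 0.09 and conclude that timing accounts for 6% to 23%. That mixes the variance of a gain with the variance of a level, and the document's endpoint is the level.

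**The document's speeds do not measure the effect.** Correct. The 0.34 m/s subacute and 0.84 m/s chronic values come from different cited cohorts, and this trial takes only patients who can walk 10 m. Their 0.50 m/s gap serves above only as an assumed total rise.

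**The plan already covers part of this.** NIHSS is scored at M0 and so reflects status at entry. Adjusting for the stratification factors is coherent, and a fuller analysis plan could add covariates. Baseline speed, also absent from the list, is probably the stronger covariate. All fair; but the article states its list for both primary and secondary outcomes, and at equal baseline speed time since stroke still separates expected recovery.

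**The regression text is not closed.** The restriction to cognitive and motor variables belongs to the univariate step; the multivariable step speaks of factors in general. So the text does not exclude time since stroke, but it does not name it either.

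**The month-6 anchor.** If month 6 is counted from the stroke, time since stroke does not vary at the endpoint. Entry time then sets the interval from treatment to endpoint instead, so it remains relevant on either reading.

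**Conclusion.** The point holds in a limited form. For the primary comparison, the omission is a modest loss of precision whose size the documents do not fix. For time since stroke alone it is about 0 to 1.4% of variance, less than one power point, assuming uniform entry, a common curve with a 0.50 m/s total rise, and a first-half rise at least three times the second. The gain to 79.0–86.5% power rests on an assumed R2 of 0.02 to 0.20, with the upper part credible mainly alongside baseline speed. Bias in the treatment contrast is not supported.

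The firmer part is the regression of gait-speed increment. Its predictors are not randomized and its outcome depends directly on remaining spontaneous recovery, so leaving out time since stroke invites confounded determinants. The direction and size of that confounding cannot be derived from the document.

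**What to change.** 1. Prespecify time from stroke to randomization, continuous (for example log days), as a covariate in the primary and secondary models, together with baseline single-task 10MWT speed.
2. Force time since stroke into the multiple regression of gait-speed increment, whatever the univariate screen shows.
3. Reconcile the month-6 anchor: from stroke in Outcomes {12} and {18a}, against inclusion in the Abstract and end of program in {20a}.

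Do not add time since stroke as a stratum: 3 × 3 × 12 = 108 strata already leave 300/108 ≈ 2.8 patients each.

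The cost is wording plus one or two degrees of freedom. The stroke date and baseline speed are already collected, and randomization and visits do not change. The change should be dated before outcome data are analyzed.

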### *Sample size {14}*

According to Severinsen et al., the mean ± standard deviation 10MWT speed among stroke victims at the chronic stage is 0.84 ± 0.3 m.s^−1^ [65]. With an alpha coefficient of 0.05 (in two-tailed tests), a power of 80%, and a gait speed standard deviation of 0.3 m.s^−1^, we have calculated that a sample size of 280 patients (140 per group) will be needed to evidence a gait speed increment of 0.1 m.s^−1^ (a magnitude known to be clinically relevant after stroke [66–69]).

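### The primary comparison of M6 gait speed does not adjust for M0 gait speed, which is measured before randomization; this costs precision but does not bias the comparison

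*Protocol article*

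**What the plan says.** The Statistical methods section (item 20a) defines the endpoint as a single follow-up value: "The primary outcome measure will be the ST 10MWT result 5 months after the end of the GR protocol". It is not a change score, so baseline does not enter that way. The comparison is made after adjustment for "age, center and the NIHSS score in an analysis of covariance (ANCOVA"), and the test is then left open, depending on the type of data, between a t-test, a Mann-Whitney test and a generalized linear mixed model. For the secondary outcomes the adjustment set is again "age, center, and NIHSS score (in an ANCOVA").

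Baseline speed is available. The section on clinical assessments at baseline lists "the single-task 10-m walking test (ST 10MWT"), and Table 3 ticks this test at M0, M1, M2 and M6. Eligibility requires "ability to walk at least 10 m (with or without a technical aid) at a speed below 1.2" m/s. Sequence generation (item 16a) places randomization after the M0 assessments. It also says "participants will be stratified by age (<45, 45 to 64, and ≥65"), by NIHSS band and by center. Gait speed is not a stratification factor. The three covariates are thus the three stratification factors.

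**The concern.** When an outcome is a repeat of a measurement taken before randomization, the baseline value is the natural covariate. It usually explains part of the follow-up variance that general prognostic factors do not, and conditioning on it removes the effect of any chance difference between arms at the start. Here the printed covariate list leaves it out. A statistical analysis plan that followed the article faithfully would leave it out too, so this is a stated choice and not a detail deferred to another document.

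Precision is at stake. The sample size rests on the full between-patient SD and has no reserve, so a covariate already on file is a cheap way to narrow the confidence interval for the primary result.

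**Working it through.** **Inputs from the protocol.** Sample size (item 14): "With an alpha coefficient of 0.05 (in two-tailed tests), a power of 80"%, with "a gait speed standard deviation of 0.3" m/s and a difference of 0.1 m/s, giving 140 per group. Recruitment (item 15): 300 enrolled, 150 per group, with 10% expected loss, so 150 × 0.9 = 135 analysed per arm.

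**Inputs not in the protocol (assumed).** The share of M6 variance explained by age, center and NIHSS (R²) is taken as 10%, 20% or 30%. The partial correlation of M0 with M6 speed given those covariates (r) is taken as 0.3, 0.5 or 0.7.

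**Step 1: reproduce the plan's figure.** n per arm = 2(1.960 + 0.842)² × 0.3² / 0.1² = 141.3, so 142 per arm or 284 in total, against 280 stated. This agrees to within 3%. The calculation uses the raw SD, with no allowance for any covariate.

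**Step 2: power with no adjustment.** Two-sided noncentral t: 79.4% at 140 per arm and 77.9% at 135 per arm (79.6% and 78.2% by the normal approximation).

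**Step 3: power of the planned ANCOVA, then with M0 speed added.** The residual SD is 0.3 × √(1 − R²) for the planned covariates, multiplied by √(1 − r²) once M0 speed is added. At 135 per arm, noncentral t:

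| R² of age, center, NIHSS | Residual SD, planned | Power, planned | Power, r = 0.3 | Power, r = 0.5 | Power, r = 0.7 |
|---|---|---|---|---|---|
| 10% | 0.285 | 82.0% | 85.4% | 91.3% | 98.1% |
| 20% | 0.268 | 86.2% | 89.2% | 94.1% | 99.0% |
| 30% | 0.251 | 90.4% | 92.8% | 96.5% | 99.5% |

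Example, first row at r = 0.5: 0.3 × √0.90 = 0.2846; 0.2846 × √0.75 = 0.2465; standard error 0.2465 × √(2/135) = 0.030 m/s, against 0.2846 × √(2/135) = 0.035 m/s without M0 speed.

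Removing 14 degrees of freedom for the covariates (11 for 12 centers, and one each for age, NIHSS and M0 speed) lowers the with-M0 figures by less than 0.1 percentage point.

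**Step 4: gain over the planned analysis.** At r = 0.3 the gain is about 2 to 3 points. At r = 0.7 it is about 9 points (R² = 30%) to 16 points (R² = 10%). Whatever R² is, the standard error shrinks by the factor √(1 − r²): 0.95, 0.87 and 0.71 for r = 0.3, 0.5 and 0.7.

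**The case against.** The case for the plan as written has real force. Adjusting for the stratification factors is a legitimate analysis that matches the design. Omitting a prognostic covariate neither biases a randomized comparison nor inflates the type I error. The stated 80% power was computed on the raw SD and never relied on baseline speed. The fall to about 78% at 135 per arm comes from enrolling 300 when 280/0.9 would need about 312, which is a separate matter. The mixed model that the plan allows could also carry M0 speed, although no section says that it would.

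All of that stands, and it limits the point to efficiency. Four stronger readings are tempting but unsupported:

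- **That the comparison is biased.** It is not. Chance imbalance averages to zero over randomizations, and its variability is already in the standard error. For example, with an M0 SD of 0.3 (assumed; no M0 SD is given), a one-standard-error imbalance is 0.3 × √(2/135) = 0.037 m/s. Carried forward with an assumed slope of 0.6 it is 0.022 m/s, which is 0.6 of the unadjusted M6 standard error. It is not a harm on top of the lost precision.
- **That M0 speed is the strongest predictor of M6 speed.** This is plausible for the same test in the same patient, but the protocol compares no predictors. It also gives grounds for caution: entry speed is capped by eligibility, and patients enter at any time within 6 months of stroke, so later recovery will vary. The test-retest reliability quoted for the 10-m test is not a 6-month correlation.
- **That M0 speed would lift power from 78% to well above 90%.** That credits it with variance that age, center and NIHSS may already explain. The fair comparator is the planned ANCOVA.
- **That the M0 data go unused.** Baseline comparisons are planned, and the regression on the increment in gait speed needs M0 speed. The gap is only in the between-group tests.

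The objection does not explain why a pre-randomization measurement of the endpoint itself is left out of a covariate list that the article prints.

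**Conclusion.** The point holds as a loss of efficiency that should be corrected, not as a threat to validity. The named adjustment set omits M0 gait speed from the primary between-group analysis, and omits each outcome's own M0 value from the secondary ones. At 135 per arm, SD 0.3 m/s and a difference of 0.1 m/s, the planned ANCOVA has about 82-90% power if its covariates explain 10-30% of the variance. Adding M0 speed raises this to about 85-98% at the lower end and 93-99.5% at the upper end, for partial correlations of 0.3 to 0.7. R² and r are both assumptions, because the protocol gives neither. The gain may be as small as 2 to 3 points; the direction is not in doubt unless the partial correlation is close to zero. If the t-test or Mann-Whitney test is run on raw M6 speed, no covariate is used, and the unadjusted 77.9% is the relevant t-test figure.

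**What to change.** Before database lock, prespecify one primary model: M6 speed = arm + M0 ST 10MWT speed (continuous) + age + NIHSS + center. Fit it as an ANCOVA, or as a mixed model with the same baseline covariate. State that it replaces the data-dependent choice that includes the t-test and the Mann-Whitney test; otherwise the new covariate may never be used. For each secondary outcome measured at M0 and compared between arms, add its own M0 value to the model.

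The cost is a short change to the statistical section and one degree of freedom per model. No new data, visits or patients are needed.
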